**Samples stored for future research**

A whole blood sample and a hair sample will be collected at the follow up visit at the end of the trial and will be kept for future analyses at the Wolfson Institute laboratory. Whilst not all analyses can be anticipated at present, these might, for example, include analysis of drug metabolites in the hair sample. Consent for this will be sought.

***4.6 Schedule of Assessment***

| **Procedure** | **Day 0a** | **Weeks**  **1-2** | **Weeks**  **3-4** | **Weeks**  **5+** | **Follow up** |
| --- | --- | --- | --- | --- | --- |
| Consent | x |  |  |  |  |
| Medical History | x |  |  |  |  |
| Blood Pressureb | x |  |  |  | x |
| Blood sample for serum Cholesterol | x† |  |  |  | x |
| Hair sample |  |  |  |  | x |
| Text message sent daily |  | x |  |  |  |
| Text message sent every alternate day |  |  | x |  |  |
| Text message sent weekly |  |  |  | x |  |
| Text message sent monthly |  |  |  |  |  |
| Extra text message if necessary |  | x | x | x |  |
| Telephone call if necessary |  | x | x | x |  |
| Questionnaire on Adherence |  |  |  |  | x |
| *Prescription refill ascertainment |  |  |  |  | x |

a: Day 0 = Day of randomisation

b: Two blood pressure readings will be performed, and the mean recorded.

† part of routine care

**** possible additional assessment, if practical***

**5.** **STUDY ENDPOINTS**

***5.1 Primary end-point***

The primary endpoints are:

1. Continuation rate: The proportion of patients in each arm remaining on combination therapy at the end of follow-up.*
2. Number of days in the last month of the study that patients missed taking their medication.

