 **Date: 10 Nov 2010**

**Site:** Wolfson Institute of Preventive Medicine, Barts and the London School of Medicine, Queen Mary & Westfield College, University of London

| **TITLE** | **Investigation of Text Reminders on Adherence to Cardiac Treatment** |
| --- | --- |
| **SHORT TITLE** | INTERACT Study |
| **Protocol Version Number and Date** | Version 3 [ May 01 2012] |
| **Methodology** | Randomised controlled trial |
| **Study Duration** | 18 months |
| **Co-ordinating Centre** | **Wolfson Institute of Preventive Medicine** |
| **Objectives** | To assess the effect of programmed text message reminders on adherence to cardiovascular disease preventive medication. |
| **Number of Subjects/Patients** | 300 |
| **Main Inclusion Criteria** | Patients prescribed lipid lowering and/or blood pressure lowering medication. |
| **Intervention** | “Text Message Programme (TMP)”: periodic text messages, adapted in frequency to the responses received coupled with telephone or clinic consultation to resolve non-adherence. |
| **Outcome Measures** | **Primary**: Non-adherence to combination therapy  **Secondary**: serum cholesterol, blood pressure and cost-effectiveness |
| **Statistical Methodology and Analysis** | To estimate the absolute and relative differences (and 95% confidence intervals) in non-adherence to preventive therapy in the intervention and control arms, 6 months after enrolment in the study. Based on 30% non-adherence rate in the control arm and a 20% loss-to-follow up, a study of 300 participants has 80% power to detect a 50% reduction in non-adherence from TMP at the 5% level of significance. |

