**Appendix E Text 23**

**Appendix F Letter 24**

**1. INTRODUCTION**

***1.1 Abstract***

A randomised controlled trial of text message reminders will be conducted in 300 patients who are receiving combination therapy with at least one lipid lowering drug (eg. a statin) and/or one blood pressure lowering drug (eg. an ACE-inhibitor). The intervention arm will consist of a “Text Message Programme” – periodic text messages asking whether patients have taken their medication, adapted, over time in their frequency, to the responses received, coupled with telephone or clinic follow-up to resolve reasons for non-adherence. The control group will receive standard care. Non-adherence to therapy (discontinuing one or more of the starting combination) will be assessed at 6 months by questionnaire. Serum cholesterol and blood pressure measurement will be undertaken as independent, objective measures of drug use. Allowing for a 20% loss-to follow up, the study has 80% power to identify a statistically significant reduction in non-adherence of 50% in the intervention group at a 0.05 level of statistical significance.

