**2.2 Study Objectives**

**Primary Objective**: to determine, in each randomised group, non-adherence to combined treatment with lipid lowering and/or blood pressure lowering treatment (Combination Therapy).

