**6. STATISTICAL CONSIDERATIONS**

***6.1 Number of Participants***

The TMP is expected to reduce non-adherence by 50%. Non-adherence among patients with angiographically confirmed coronary artery disease has been reported to be at least 50%3. To be conservative we have taken the non-adherence rate in the control arm to be 30%. A study of 300 participants would have 80% power to detect a 50% reduction in non-adherence at the 5% level of significance. This allows for a 20% loss-to-follow up.

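### Section 5.1 names two primary endpoints, while the synopsis, abstract, objective and sample size use one; the stated 5% and 80% cover only that one

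*Protocol*

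**What the plan says.** Protocol section 5.1 opens in the plural, "The primary endpoints are", and lists two items. The first is the continuation rate: "The proportion of patients in each arm remaining on combination therapy at the end of follow-up". The second is "Number of days in the last month of the study that patients missed taking their medication". The notes under 5.1 explain how to classify a patient by drug class at follow-up, which concerns the first item only.

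The rest of the protocol has one primary outcome:

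- The synopsis gives it as "Non-adherence to combination therapy", and its statistics row plans differences and 95% confidence intervals for that outcome 6 months after enrolment.
- The abstract (1.1) defines it: "Non-adherence to therapy (discontinuing one or more of the starting combination) will be assessed at 6 months by questionnaire".
- The primary objective (2.2) is non-adherence to combined treatment. Missed days are not mentioned.
- Section 6.1 sizes the trial on it: "A study of 300 participants would have 80% power to detect a 50% reduction in non-adherence at the 5% level of significance". The control rate is taken as 30%, and 20% loss to follow-up is allowed for.

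Section 6.2 refers to differences in adherence, cholesterol and blood pressure, and does not settle which outcome is primary. No mean, standard deviation or target difference for days missed appears anywhere in the protocol.

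**The concern.** The continuation rate is the complement of non-adherence, so the first item in 5.1 agrees with the rest of the protocol. The second does not. Days missed is a count with a different meaning: a patient still on both drug classes who missed 20 days in the last month is adherent under the notes to 5.1, yet does badly on days missed. The two can therefore point in different directions, with continuation unchanged and fewer days missed, or the reverse.

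Someone writing the analysis from this protocol would have to choose between 5.1 and the synopsis, abstract, objective and 6.1. If that choice were made after the results were seen, the meaning of a positive trial would depend on them. The error rate and power for the primary question would also depend on a rule that the protocol does not give.

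**Working it through.** **Inputs.** Control non-adherence 30% (6.1); 50% relative reduction, so 15% in the intervention arm (6.1 and flow diagram); level 5% and power 80% (6.1); 300 patients at 1:1 (6.1, 4.4); 20% loss (6.1), so 300 × 0.8 = 240 evaluable, 120 per arm. Sidedness is not stated; two-sided is assumed because 95% confidence intervals are planned.

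**1. The protocol's own figure.** Normal test of two proportions, pooled variance under the null, no continuity correction. The mean proportion is (0.30 + 0.15)/2 = 0.225.

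- Null term: √(2 × 0.225 × 0.775) = 0.5906.
- Alternative term: √(0.30 × 0.70 + 0.15 × 0.85) = √0.3375 = 0.5809.
- n per arm = [(1.960 × 0.5906 + 0.842 × 0.5809)/0.15]² ≈ 120.5, rounded up to 121. The total is 242, and 242/0.8 = 302.5, rounded up to 303.
- Power at 120 per arm = Φ[(0.15 × √120 − 1.960 × 0.5906)/0.5809] = Φ(0.836) = 79.8%.

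So 300 patients and 80% power are reproduced for the single binary endpoint.

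**2. Either endpoint counts, each at 5%.** If the two tests are independent, the chance of at least one false claim is 1 − 0.95² = 9.75%. If they are correlated, it is 1 − P(|Z₁| ≤ 1.96 and |Z₂| ≤ 1.96) under a bivariate normal distribution. The correlations below are assumptions, since the protocol gives none.

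| Correlation of the two tests | False-claim rate |
| --- | --- |
| 0 | 9.75% |
| 0.5 | 9.1% |
| 0.7 | 8.35% |
| 0.9 | 7.0% |

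Under this rule the chance of at least one success does not fall below 79.8%; the cost is in error rate only.

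**3. Level split, 2.5% each.** The critical value becomes 2.241. Power for continuation = Φ[(0.15 × √120 − 2.241 × 0.5906)/0.5809] = Φ(0.550) = 70.9%. Restoring 80% needs 147 per arm, 294 evaluable, and 294/0.8 = 367.5, so 368 randomised.

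**4. Both required, each at 5%.** The error rate does not exceed 5%. Joint power cannot exceed that of the first endpoint, 79.8%. If days missed also had 80% power (assumed), joint power would be 0.798 × 0.80 = 64% under independence and 73% at correlation 0.8. The actual figure cannot be computed, because the protocol gives no planning values for days missed.

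**5. One primary endpoint, or a fixed sequence with continuation first at 5%.** The level stays at 5% and power for continuation stays at 79.8% with 300 patients.

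**The case against.** The strongest reply is that 6.1 is not wrong. It claims its power and level for non-adherence alone, and the calculation bears it out. A reader might infer from two undivided primary endpoints that the 5% level is in fact exceeded and the 80% power in fact lost. The document does not support that. The inflated error rate needs an either-or rule, which the protocol never states. The loss of power to 70.9% needs a split of the level, which is a different rule. The two losses are alternatives, and a fixed sequence incurs neither.

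Three further points have weight. A rule for handling two primary endpoints is commonly left to the statistical analysis plan, which is not at hand, so its absence from the protocol is not itself a fault. The protocol also hints at which endpoint leads: continuation is listed first, only it has classification notes, and the trial is sized on it. And 9.75% is the independence case, which is unlikely here, since a patient who has stopped a drug would probably also report missed days.

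All of this limits what can be said about size, but it does not remove the contradiction. The number and identity of the primary endpoints belong to the protocol. The hints favour one endpoint, yet 5.1 expressly makes days missed primary as well, and no written order overrides it.

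**Conclusion.** The contradiction stands: two primary endpoints in 5.1, one in the synopsis, abstract, objective and sample size. The 5% and 80% in 6.1 are sound for non-adherence and are not assured for the pair. It would go too far to say that they fail, because which of them suffers, if either, depends on a decision rule that the protocol does not give.

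The possible size runs from no loss (single primary or fixed sequence), through a false-claim rate of 7.0% to 9.75% (either-or, assumed correlations 0.9 to 0), to power of 70.9% for continuation (split level) or at most 79.8% jointly (both required). These figures rest on two-sided normal tests, 120 evaluable patients per arm and the protocol's own 30% against 15%.

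**What to change.** In 5.1, name one primary endpoint: non-adherence (1 minus the continuation rate) at 6 months, with the existing classification notes. Move days missed in the last month to 5.2 as a secondary endpoint. Alternatively, keep both in 5.1 and state a fixed sequence: continuation first at 5%, and days missed tested at 5% only if continuation is significant. Either brings 5.1 into line with the sample size in 6.1 and keeps 5% and about 80% with 300 patients. The choice should be recorded before outcome data are examined.

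The cost is a few lines in 5.1, plus 5.2 if days missed is moved there, with no extra patients or data. The downside is that days missed can no longer support the trial's primary claim on its own. If the sponsor prefers a split level or a both-required rule, that rule has to be stated and the trial re-sized, which for the both-required rule also needs planning values for days missed that the protocol does not contain.

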****NB:***

***If the patient started on two classes (e.g. lipid lowering plus blood pressure lowering) and is taking only one (e.g. lipid lowering) at follow-up they would be non-adherent.***

***If the patient started on one class (eg. lipid lowering) and is taking none at follow-up they would be non-adherent.***

***If patients change drugs within the same class they would remain adherent.***

***i.e. if the starting treatment included lipid lowering (simvastatin) and blood pressure lowering (lisinopril) and the follow-up regimen included atorvastatin (lipid lowering) and losartan (blood pressure lowering), then the patient would have adhered to starting regimen.***

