**3. STUDY POPULATION**

***3.1 Inclusion Criteria***

Participants will be men and women of all ages who own a mobile phone with text message capability. Patients will be on a combination of medicines (at least a lipid lowering drug and/or a blood pressure lowering drug) for cardiovascular disease preventive treatment.

It is anticipated that most patients will be on both classes of drug (since these are recommended for cardiovascular disease prevention). However patients who for some reason are only on one class (eg. they may be intolerant of all blood pressure lowering drugs) will still be eligible and non-adherence to the one class will be assessed.

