**Other measurements**

Each patient will be questioned at the end of the study to assess non-adherence to their combination therapy prescribed at the start of the trial. Adherence will be assessed by asking the patient the following questions:

1) Are you still taking your i i) Cholesterol lowering drug (eg. statin) ii) Blood pressure lowering drug? (eg. lisinopril)

2) In the past month were there any days when you did not take your medication?

3) If so, how many days did you not take your medication?

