**Appendix B: GP Letter**

Centre for Environmental and Preventive Medicine

| WOLFSON INSTITUTE OF PREVENTIVE MEDICINE  Director: [name] Wald FRCP FRS | [name] |
| --- | --- |

[contact]

[contact]

E-mail: [[contact]](mailto:[contact])

GP Name and Address

RE: Patient Name, date of birth

Dear Dr …….,

I am writing to let you know about a randomised trial being carried out at Barts and the London School of Medicine, and to say that your patient (above) has agreed to take part.

We are examining the value of a text message programme (TMP) on reducing non-adherence to cardiovascular preventive medication among patients who are prescribed the lipid lowering drug and/or a blood pressure lowering medication.

We have made it clear that the decision to participate is entirely voluntary.

Each patient randomised to the TMP arm of the trial will receive periodic text messages to determine whether they have taken their cardiac medication. Patients who do not respond or whose response is that they have been unable to take their medication will be telephoned by a study doctor or pharmacist to explore and resolve the reason why medication is not being taken as prescribed. If the problem can not be resolved by phone (e.g. a side effect develops that requires a change in therapy) we will advise the patient to make an appointment with you at your general practice. We will write to you explaining the patient’s particular problem, and send a copy of the letter to the patient.

The TMP is therefore, not only a means of reminding patients to take their medication, it is also a method for identifying those patients who, for whatever reason, have discontinued their treatment, so that medical assistance can be quickly offered to resolve the problem.

I enclose a study information leaflet which has been given to your patient. Please do not hesitate to contact me if you wish to know anything further about the study.

Yours sincerely,

[name]

Consultant Cardiologist and Senior Lecturer

Barts and The London

School of Medicine and Dentistry

University of London

INTERACT

Version 1, 10 November 2010

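### The first primary endpoint measures all-cause discontinuation but is called non-adherence, and the questionnaire does not record who stopped the drug

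*Protocol*

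**What the plan says.** **Scoring rule.** The notes to section 5.1 of the protocol judge the patient against the classes taken at the start. Someone who began on two classes and "is taking only one (e.g. lipid lowering) at follow-up they would be non-adherent". For a single starting class the rule is "If the patient started on one class (eg. lipid lowering) and is taking none at follow-up they would be non-adherent". There is one exception: "If patients change drugs within the same class they would remain adherent". The abstract (section 1.1) agrees: "Non-adherence to therapy (discontinuing one or more of the starting combination) will be assessed at 6 months by questionnaire". None of these rules depends on the reason for stopping or on who decided it.

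**Label.** Section 5.1 names this endpoint a continuation rate. The summary table, section 2.1 and section 2.2 state the target as non-adherence, and the notes to 5.1 call the patients concerned non-adherent.

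**Data collected.** Section 4.5 (Other measurements) sets out to "assess non-adherence to their combination therapy prescribed at the start of the trial". It asks three things: whether each class is still taken, whether any days were missed in the past month, and how many.

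**Contact by arm.** Under the text message algorithm in section 2.4, a reply of no, or no reply, leads to a call from the study coordinator. A possible side effect goes to a study pharmacist or doctor. A problem that cannot be solved by phone leads to advice to see the GP, with a letter. The GP letter (Appendix B) gives as its example that "a side effect develops that requires a change in therapy". Controls have standard care, which the footnote to the flow diagram describes as hospital clinic review, GP consultations and community pharmacist review.

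**The concern.** A patient who stops a class because a prescriber said so, and gets no replacement from that class, has followed advice but is scored as non-adherent. The protocol foresees such patients. Section 3.1 accepts people on one class at entry because "they may be intolerant of all blood pressure lowering drugs", and Appendix B expects side effects during follow-up.

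If these stops were rare and equal in the two arms, the label would be loose and the effect somewhat diluted. What raises the stakes is that the TMP is designed to find treatment problems and pass them to professionals, so the intervention may itself change how often prescribers withdraw a class. A difference between arms, or the lack of one, could then mix two things that a reader would want apart: patients giving up treatment, and prescribers ending it.

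A later analysis plan could not settle this, because no planned item records who stopped the drug in both arms.

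**Working it through.** **1. How the rule sorts patients.** Reading section 5.1 and its notes against the possible histories:

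| What happened to a starting class | Scored as | Would the section 4.5 questions reveal who decided? |
| --- | --- | --- |
| Patient stopped it | Non-adherent | No |
| Prescriber withdrew it, no replacement | Non-adherent | No |
| Changed to another drug of the same class | Adherent | Not needed |

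The first two rows cannot be told apart in the data.

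**2. Other sources.** The letters to GPs (section 2.4) and the GP and clinic contacts logged for costing (section 6.2) relate mainly to the TMP arm. Prescription refill ascertainment is marked in section 4.6 as possible only if practical, and nothing says it would show who ended a drug. None of these gives a like-for-like comparison of the arms.

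**3. The plan's own power figure.** Inputs from section 6.1: control rate 30%, 50% reduction (so 15%), 5% level (taken as two-sided), 300 patients, 20% loss. With 1:1 allocation (section 4.4), 150 × 0.80 = 120 assessed per arm.

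Power = Φ[(d − 1.96 × s0) / s1], where d = p1 − p2, s0 = √(2p̄(1 − p̄)/n), s1 = √((p1(1 − p1) + p2(1 − p2))/n), and p̄ is the mean of p1 and p2.

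For 30% v 15%: s0 = 0.0539, s1 = 0.0530, (0.15 − 1.96 × 0.0539)/0.0530 = 0.836, power 79.8%. The stated 80% reproduces.

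**4. Illustration.** The documents give no rate of prescriber withdrawal. Assume that the TMP adds 1.5 or 3 percentage points of such stops to its planned 15% and that the control rate stays at 30%:

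| TMP rate | Relative reduction | s0 | s1 | Power, 120 per arm |
| --- | --- | --- | --- | --- |
| 15% (plan) | 50% | 0.0539 | 0.0530 | 80% |
| 16.5% | 1 − 16.5/30 = 45% | 0.0545 | 0.0538 | 70% |
| 18% | 1 − 18/30 = 40% | 0.0551 | 0.0546 | 59% |

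**5. Equal stops in both arms.** If 3 points were added to each arm (33% v 18%), the relative reduction would be 1 − 18/33 = 45% and power 76%. Some dilution can occur without any difference between arms, but it is much smaller.

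**6. Removing such stops from the primary definition.** Suppose 5 of the 30 control points were prescriber stops (an assumption). If the 50% reduction held for the rest, 25% v 12.5% gives power 70%. If instead 5 points left each arm, 25% v 10% gives 87%. The effect on power of redefining the endpoint can go either way.

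**The case against.** The strongest reply is that all-cause continuation is a legitimate endpoint and that the protocol chose it. Section 5.1 uses the term continuation rate, section 1.1 defines non-adherence as any discontinuation, and section 2.1 speaks of treatment stopped for any reason. This also fits the cholesterol, blood pressure and life-years outcomes, which depend on whether the drug is taken. That stands, and it is why the rule should stay. It does not supply the missing information on who stopped the drug, or remove the mismatch with the stated target.

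A reader might infer that only TMP patients have a route to a prescriber, or that the intervention manufactures its own endpoint events. The documents do not support either:

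- Controls reach prescribers through standard care. Only the study-driven contact is extra.
- The sample text asks whether medication was taken. Problems are explored only in the call that follows a no or silence, and some of those called will already have stopped and would count anyway.
- Appendix B speaks of a change in therapy, not withdrawal. Handling side effects may turn would-be stoppers into within-class switchers, who count as adherent. That offsets the bias.
- The 1.5 to 3 points have no source, and the planned 50% reduction may already be net of such stops.

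A reader might also infer that prescriber-stopped classes should be scored as adherent in the primary analysis. That would put the main result on self-reported attribution by patients who know their arm. TMP patients, after calls and copied letters, may more readily say that a professional stopped the drug, which could favour the TMP.

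**Conclusion.** The point holds as a gap in labelling and data collection. As written, the trial cannot separate patient non-adherence from withdrawal on medical advice, and the TMP's extra route to professionals gives a reason why the latter may differ by arm. The likelier direction is against the TMP, which threatens power and interpretation more than it risks a false positive. The net direction and size cannot be derived from the documents.

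The fall in power from 80% to 70% or 59% shows only how sensitive the design would be. It rests on the assumed 1.5 to 3 extra points in the TMP arm, an unchanged control rate, a two-sided test and 120 assessed per arm. It is not an estimate.

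Only the first of the two primary endpoints is clearly affected. The second, "Number of days in the last month of the study that patients missed taking their medication", is not governed by the class rule, although it is unclear how a drug stopped on advice would be counted there. This is a cheap improvement, worth making because the information cannot be recovered in both arms once the visits are over.

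**What to change.** 1. In section 4.5, add to the first adherence question, in both arms and for each class no longer taken: did a health professional stop it, or did the patient?
2. Keep the any-reason rule in section 5.1 as the primary definition, and describe it there and in the objectives as all-cause discontinuation of a starting class.
3. Pre-specify a sensitivity analysis in which a class withdrawn by a prescriber does not count as non-adherence.
4. Report prescriber withdrawals by arm.

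The cost is one short item at a visit already planned, a wording change and one extra analysis. The answer is self-reported by patients who know their allocation, so it should inform interpretation and not drive the primary result.
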